### 3.6. Effectiveness Measure

The primary effectiveness measure for the cost-utility analysis will be quality-adjusted life years (QALYs), calculated from EQ-5D-5L utility scores collected at baseline, week 3–4, week 12, and week 24. Singapore-specific value sets will be applied to convert EQ-5D-5L health states to utility weights [46]. QALYs will be calculated using the area-under-the-curve method with linear interpolation between assessment points. For historical controls, EQ-5D-5L data will be extracted from the TTSH registry where available; if unavailable, utility values will be mapped from functional outcomes (FMA-UE, Barthel Index) using validated mapping algorithms [47].

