### 3.2. Economic Evaluation

An incremental cost–utility analysis (CUA) will be conducted alongside the feasibility study to generate exploratory cost data of BCI rehabilitation compared to standard care, acknowledging the limited precision afforded by the single-arm design. The economic evaluation will adopt a healthcare system perspective over a 24-week time horizon, consistent with the clinical follow-up period.

To keep the economic evaluation focused, it is organized around two scopes: (1) the within-trial 24-week cost–utility analysis from a healthcare-system perspective described above and (2) a secondary long-term extrapolation. For the latter, a cohort state-transition (Markov) model, structured around post-stroke functional health states (for example, FMA-UE severity together with functional dependency) and an absorbing death state, will project costs and quality-adjusted life years over 2-year and 5-year horizons, using an annual cycle with half-cycle correction and discounting at 3% per annum (0% and 5% in sensitivity analysis), consistent with Singapore health-technology-assessment norms. Transition probabilities and utilities will be derived from the trial, the TTSH registry, and the published literature; a societal perspective incorporating productivity losses and informal caregiver time will be explored as a sensitivity analysis rather than as a primary scope. As it remains uncertain whether clinical gains from BCI-rehabilitation are sustained into the chronic phase beyond the trial follow-up period, all estimates extrapolated beyond 24 weeks will be treated as exploratory and interpreted with caution. Structural and parameter uncertainty will be characterized through deterministic and probabilistic sensitivity analyses, reported in accordance with CHEERS 2022.

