### 3.3. Comparator Group: Historical Controls

Given the single-arm feasibility design, the comparator group will be derived from the TTSH stroke rehabilitation registry (2017–2025). Historical controls will be propensity-matched to BCI participants based on (1) baseline FMA-UE score, (2) age, (3) stroke type (hemorrhagic vs. ischemic), and (4) time post-stroke at rehabilitation admission (2–12 weeks). To reduce residual confounding, the propensity model will additionally include sex, baseline functional status (admission FIM and MBI), comorbidity burden (Charlson Comorbidity Index), clinically relevant concomitant medications (for example antispasticity and mood-active agents), the total inpatient rehabilitation therapy dose, and the calendar year (era) of admission. Historical control data will be obtained from an institutional inpatient stroke rehabilitation cohort assembled between 2022 and 2025 (more than 100 patients), for which baseline and discharge EQ-5D-5L utilities and FMA-UE scores are available to support propensity matching and quality-adjusted life year estimation. Corresponding inpatient rehabilitation cost data will be obtained from hospital administrative and costing databases. FMA-UE categories may use severe impairment (FMA-UE 0–19) and moderate-to-mild impairment (FMA-UE 20–47). This approach has been previously validated in the TTSH setting for evaluating upper extremity recovery outcomes [40]. Matching will be performed using nearest-neighbor propensity score matching with a caliper of 0.2 standard deviations to ensure adequate balance on baseline covariates. The matching ratio will be 1:3 (BCI/control) to maximize statistical power while maintaining adequate matching quality. Balance diagnostics will be assessed using standardized mean differences (target < 0.1 for all covariates) and variance ratios. To limit temporal confounding arising from the eight-year registry window (2017–2025)—over which ward staffing, rehabilitation protocols, and case-mix may have changed—the primary comparator analysis will be restricted to the contemporaneous 2022–2025 inpatient cohort, calendar year will be included as a matching and adjustment covariate, and models will additionally be fitted with admission era as a fixed effect; the influence of the matching window will be examined in sensitivity analyses that progressively restrict controls to narrower, more recent time bands. Sensitivity analyses will explore alternative matching specifications, including different caliper widths and matching algorithms (genetic matching, coarsened exact matching) to assess robustness of findings to matching choices. If precise stroke onset dates are unavailable for historical controls, hospital arrival date will be used as a proxy, consistent with Singapore Stroke Registry methodology.

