### 3.9. Sensitivity and Uncertainty Analysis

Deterministic sensitivity analyses will be conducted to assess the robustness of results to parameter uncertainty, including variations in (1) equipment costs (purchase vs. rental models), (2) therapist time costs, (3) discount rates (0% and 5% annually), and (4) utility mapping assumptions for historical controls. Probabilistic sensitivity analysis using Monte Carlo simulation (5000 iterations) will characterize joint parameter uncertainty and generate cost-effectiveness acceptability curves showing the probability of BCI being cost-effective across a range of willingness-to-pay thresholds. An additional scenario analysis will model partial supervision—approximately 25%, rather than 50%, of sessions unsupervised from the midpoint of training following initial orientation, acknowledging this proportion may vary in practice—to assess the minimum substitution level required for a favorable incremental cost-effectiveness ratio.

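### Mapping utilities for controls only lets any gap between mapped and measured EQ-5D-5L enter the QALY difference as if it were a treatment effect

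*Protocol article*

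**What the plan says.** Protocol section 3.6 makes QALYs the primary effectiveness measure of the cost-utility analysis. For BCI participants they are "calculated from EQ-5D-5L utility scores collected at baseline, week 3–4, week 12, and week 24". For the comparator, "For historical controls, EQ-5D-5L data will be extracted from the TTSH registry where available"; and "if unavailable, utility values will be mapped from functional outcomes (FMA-UE, Barthel Index) using validated mapping algorithms". The fallback is written for controls only. On the method, "QALYs will be calculated using the area-under-the-curve method with linear interpolation between assessment points".

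Section 3.2 sets a "healthcare system perspective over a 24-week time horizon, consistent with the clinical follow-up period". Section 3.7 defines the ICER as the difference in mean costs over the difference in mean QALYs, with no adjustment for the source of the utility, and gives a willingness-to-pay range of SGD 50,000–100,000 per QALY.

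Section 3.3 limits how often mapping should be needed. It says that "the primary comparator analysis will be restricted to the contemporaneous 2022–2025 inpatient cohort" and describes that cohort as one "for which baseline and discharge EQ-5D-5L utilities and FMA-UE scores are available to support propensity matching and quality-adjusted life year estimation". It lists no control utility after discharge.

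Section 3.9 includes "utility mapping assumptions for historical controls" among the deterministic sensitivity analyses.

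**The concern.** FMA-UE measures arm motor impairment, and the Barthel scores measure independence in daily activities. A utility predicted from them need not have the same mean as one measured by EQ-5D-5L in the same patients. If both groups were handled the same way, a common gap would cancel in the difference. Here only controls can be mapped, so the gap stays in full. Propensity matching does not help, because it balances baseline covariates and not the way the outcome is measured.

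The denominator of the ICER is a utility difference accumulated over less than half a year, so it is likely to be small. An artefact of similar size could hide most of a real gain or make one look much larger. Section 3.2 also draws utilities for the Markov model from the trial and the registry, so the mismatch may carry into the 2-year and 5-year projections. The list of limitations in section 3.10 does not mention the difference in utility source.

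**Working it through.** The protocol states no utility, QALY or ICER figure, so there is nothing to reproduce. The check asks how large a one-sided gap becomes once it passes through the protocol's own QALY method.

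**Inputs from the protocol**
- Visits at weeks 0, 3–4, 12 and 24 (section 3.6)
- Linear interpolation, area under the curve (section 3.6)
- Horizon of 24 weeks (section 3.2)
- SGD 50,000–100,000 per QALY (section 3.7)
- Control EQ-5D-5L at baseline and discharge (section 3.3)

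**Assumptions**
- A constant gap b (mapped minus measured utility) of 0.02 to 0.05. The documents give neither its size nor its sign.
- The control discharge value stands in for the week 3–4 visit, so that only weeks 12 and 24 would be mapped.

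**Step 1: weight of each visit.** Under linear interpolation a visit carries half of each adjacent interval.
- Visits 0/4/12/24: 2, 6, 10 and 6 weeks. Weeks 12 and 24 together carry 16/24 = 67%.
- Visits 0/3/12/24: 1.5, 6, 10.5 and 6 weeks. Weeks 12 and 24 together carry 16.5/24 = 69%.

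**Step 2: bias in the QALY difference** = b × (weeks mapped)/52, then multiplied by the threshold.

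| Visits mapped in controls | b | QALY | SGD per patient at 50,000 to 100,000 |
|---|---|---|---|
| Weeks 12 and 24 (16 to 16.5 weeks) | 0.02 | 0.0062 to 0.0063 | 308 to 635 |
| Weeks 12 and 24 (16 to 16.5 weeks) | 0.05 | 0.0154 to 0.0159 | 769 to 1,587 |
| All four (24 weeks) | 0.02 | 0.0092 | 462 to 923 |
| All four (24 weeks) | 0.05 | 0.0231 | 1,154 to 2,308 |

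These rows assume that every control is mapped at the visits named. If only a share is mapped, the bias shrinks in proportion.

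**Step 3: scale.** Suppose BCI truly raised utility by 0.05 from week 4 onward (an assumption). The true gain is 0.05 × 22/52 = 0.0212 QALY. A gap of 0.05 at weeks 12 and 24 alone is 0.05 × 16/52 = 0.0154. The estimated difference would then be 0.0212 − 0.0154 = 0.0058 or 0.0212 + 0.0154 = 0.0365 (from unrounded values), depending on the sign of the gap.

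**Step 4: same source in both groups.** If both groups are measured, or both are mapped with the same algorithm, a common b contributes b − b = 0.

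**The case against.** The strongest reply is that mapping is only a fallback and that the primary comparator was chosen from a cohort with measured EQ-5D-5L. This stands for baseline and discharge, where measured values should exist in both groups. It does not cover weeks 12 and 24: section 3.3 names no control utility there, and section 3.6 offers no route other than mapping.

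A second reply is that section 3.9 already tests the mapping. Varying it in controls alone is a fair way to see how far the ICER depends on it. But BCI values stay measured throughout, so in any analysis that uses mapped values the groups remain on different sources.

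Some stronger readings are tempting, and the documents do not support them:
- A reader might infer that the groups are measured differently in every analysis. That would require some control utility to be mapped in every analysis, which the text does not say.
- A reader might take 0.009–0.023 QALY as the expected size. It is a ceiling, because it maps all visits in all controls, contrary to section 3.3.
- A reader might add that mapped values vary less than measured ones. Even if so, lower spread alone does not bias a difference in means; it bears on the uncertainty around it.
- A reader might make much of section 3.6 naming the Barthel Index where the outcome table and section 3.3 name the Modified Barthel Index. This may be shorthand and is a minor point of wording.

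Finally, the economic evaluation is labelled exploratory, and the primary feasibility outcomes are unaffected. That limits the consequence without removing it, since the rule is stated for the main effectiveness measure of that evaluation.

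**Conclusion.** The concern holds, on condition that some control utility is mapped. In that case the gap between mapped and measured values enters the ICER denominator undiminished, and no planned analysis puts both groups on one source for the mapped visits. For the primary cohort the exposure lies mainly at weeks 12 and 24: about 0.006–0.016 QALY, or roughly SGD 310–1,590 per patient, for an assumed gap of 0.02–0.05. The direction is unknown, and the protocol calls the algorithms validated, so the gap might be smaller than assumed.

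One limit applies to the plan and the remedy alike. The protocol does not confirm that control FMA-UE or Barthel scores exist at weeks 12 and 24, so the input for mapping is itself not secured there.

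**What to change.** Amend sections 3.6 and 3.9 so that, whenever any control utility is mapped:

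1. The same algorithm is applied to BCI participants' FMA-UE and MBI at the same time points, and the QALY difference and ICER are also reported with both groups mapped.
2. Mapped values are compared with measured EQ-5D-5L wherever both exist: at the BCI visits, and at control baseline and discharge where the functional scores are also recorded.
3. A measured-only comparison is reported over the period for which controls have EQ-5D-5L, from baseline to discharge.
4. The algorithm fits the Barthel version actually recorded.

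The text should also state which control FMA-UE and MBI scores exist at weeks 12 and 24, since item 1 is possible only where they do.

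The cost is a change of wording and some extra analysis. No new BCI data are needed, because FMA-UE and MBI are already planned at the same visits. The downside is that the both-mapped result leaves out non-motor quality of life, so it should stand beside the measured analysis and not replace it.

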### 3.7. Cost-Effectiveness Analysis

The incremental cost-effectiveness ratio (ICER) will be calculated as the difference in mean costs between BCI and standard care groups divided by the difference in mean QALYs: ICER = (Cost_BCI—Cost_Control)/(QALY_BCI—QALY_Control). Results will be interpreted against the Singapore willingness-to-pay threshold of approximately SGD 50,000–100,000 per QALY gained. A secondary cost-effectiveness analysis will calculate the cost per point improvement in FMA-UE to provide clinically interpretable metrics alongside the cost-utility analysis.

### 3.8. Stratified Analysis by Baseline Severity

Given evidence that baseline motor severity substantially influences recovery trajectories [40,48], the economic analysis will be stratified by baseline FMA-UE severity using validated cutoffs: (1) severe impairment (FMA-UE 0–19) and (2) moderate-to-mild impairment (FMA-UE 20–47) [48]. These strata reflect distinct recovery trajectories and will identify subgroups for whom BCI rehabilitation may be most cost-effective. Given the small sample size (*n* = 12), these subgroup analyses are strictly exploratory, and results should be interpreted with caution.

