Existing studies, however, involved predominantly chronic stroke patients. In our recent meta-analysis of predominantly chronic stroke cohorts, BCI rehabilitation produced a mean improvement of 5.23 points on the Fugl–Meyer Assessment Upper Extremity (95% confidence interval 3.85 to 6.61; total score range 0 to 66, with higher scores indicating less impairment), exceeding the established minimal clinically important difference of 4 to 6 points for the FMA-UE [24]. We hypothesize that there may potentially be greater benefits when BCI is applied during the acute/subacute phase when neuroplasticity is heightened. Notably, an overview of systematic reviews by Liu et al. (2025) concluded that BCI-combined treatment improves upper limb motor function and quality of daily life, with effects particularly pronounced in the subacute phase [25]. In acute and subacute stroke, several studies have alluded to moderate quality evidence and high safety profile and efficacy of BCI when coupled with end effectors such as FES, VR, or robots, achieving mean FMA-UE difference of 3.69–5.02 albeit with less robust gains for ADL independence. Subgroup analyses indicated that interventions < 30 days of stroke for <3 weeks may yield greater benefits, in particular paired with FES. Optimal training parameters suggested daily sessions of 20–90 min or 2–5 times weekly for 3–4 weeks [26,27] (Figure 1).

However, practical implementation of BCI technology within acute inpatient hospital settings presents logistical challenges and must also be carefully evaluated. The setup of EEG headsets with wet electrodes requires trained personnel and can add at least 10–15 min of preparation time per session, including set-down and scalp cleansing after MI-BCI to achieve adequate electrode impedance [28,29].

Lastly, economic data remain scarce, creating barriers to widespread implementation in healthcare systems [30]. Understanding the incremental cost-effectiveness of BCI rehabilitation compared to standard care is essential for informing policy decisions regarding technology adoption and reimbursement. This study therefore incorporates a prospective economic evaluation alongside the clinical feasibility assessment to generate preliminary cost-effectiveness evidence.

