### 2.3. Eligibility Criteria

**Inclusion criteria are as follows:** adults aged 21–80 years with confirmed hemorrhagic or ischemic stroke on neuroimaging, stroke onset within 2–12 weeks; demonstrated voluntary finger flexion or extension by Oxford Medical Research Council (MRC) grade 0–4/5, Montreal Cognitive Assessment (MoCA) score > 20/30; ability to understand written and spoken instructions; and stable medical and neurological status as determined by the clinical team [34]. Because the closed-loop paradigm depends on integrating afferent (proprioceptive and visual) feedback with efferent motor intent, lesion location will be documented from neuroimaging; participants with predominantly cerebellar or brainstem lesions—who may retain intact primary sensation yet have impaired updating of internal sensorimotor (forward) models, that is, impaired predictive coding—will remain eligible but will be flagged a priori. For such participants the intervention explicitly leverages the multimodal, error-corrective feedback intrinsic to the recoveriX loop (synchronized FES-evoked movement together with visual avatar feedback) as an externally supplied source of sensory prediction; their decoding performance and clinical response will be examined as an exploratory subgroup to determine whether impaired predictive coding attenuates BCI benefit and should inform eligibility for a future definitive trial. Because the motor-imagery-related event-related desynchronization (ERD) used for BCI classification is recorded over central sensorimotor electrodes (FC3–CP4) rather than posterior/occipital sites, cerebellar lesions are not expected to directly impair this signal; ERD magnitude and BCI performance in this subgroup will nonetheless be examined exploratively as above.

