**Exclusion criteria are as follows:** previous diagnosis of stroke; implanted pacemaker or continuous infusion pump; history of seizures or epilepsy; previous neurosurgical procedures, medical instability as determined by the study team; severe blindness; anticipated life expectancy less than 6 months; hemodialysis requirement; inability to follow one-step commands; severe aphasia or dysarthria; severe arm/hand pain (Visual Analog Scale > 4/10); severe hemianesthesia or spasticity in the paretic arm (Modified Ashworth Scale greater than 2, out of 4); fixed shoulder or finger joint contractures; active arthritis in any upper limb joint; inability to tolerate upright supported sitting for at least 45 min; and disorders of consciousness or altered arousal states precluding active participation.

Written informed consent will be obtained from all participants or their legally appointed representatives, the latter group applicable to those with MoCA 21–25/30.

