### 2.4. Sample Size

Based on comparable feasibility studies in BCI stroke rehabilitation literature and recommendations from our recent meta-analysis [24], a sample of 10 subjects will be sufficient for this feasibility study. Accounting for a 20% dropout rate (*n* = 2), the final proposed sample size is 12 participants. Recruitment will aim to stratify the sample by stroke type in an approximate ratio of 40% hemorrhagic (ICH) to 60% ischemic (infarct) stroke, consistent with local case-mix.

This sample size follows established guidance for pilot and feasibility trials, in which the objective is to estimate feasibility parameters and their variability rather than to test efficacy; widely cited recommendations propose approximately 12 participants for pilot studies [35,36], and a sample of 10–12 is adequate to estimate a feasibility proportion of about 80% (for example recruitment or adherence) with a 95% confidence interval half-width of roughly ±20%. A formal efficacy-based power calculation is therefore not appropriate for the present feasibility endpoints. Nonetheless, to inform the design of a future definitive trial, an indicative a priori power calculation was performed in G*Power (version 3.1). Anchoring conservatively on 6 points—the lower end of the FMA-UE minimal clinically important difference range established largely in chronic stroke (4–6 points)—acute-stroke-specific estimates are reportedly higher, approximately 7–10 points, but 6 points was retained as a conservative estimate and the pooled effect implied by our meta-analysis (mean change 5.23 points, standard error 0.70; approximate standard deviation 3.4 in the analyzed cohorts) [24]; a two-sided paired within-group comparison (α = 0.05, power = 0.80) would require approximately 6–8 participants to detect a change of the minimal clinically important difference magnitude, whereas a two-arm parallel comparison designed to detect a 4-point between-group difference at an assumed standard deviation of 6 (Cohen’s d ≈ 0.67) would require approximately 37–46 participants per arm. The variance and recruitment-rate estimates generated by the present feasibility study will be used to refine these calculations and to power the subsequent randomized controlled trial.

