### 3.12. Data Analysis

Data analysis will be performed using Python (version 3.11; Python Software Foundation, Wilmington, DE, USA) programming language with established statistical packages. Descriptive statistics will be expressed as mean and standard deviation (SD) for normally distributed continuous variables or median with interquartile range (IQR) for non-normally distributed data. Given the small sample size characteristic of feasibility studies, non-parametric tests, including the Wilcoxon signed-rank test, will be employed for within-subject comparisons across time points. *p*-values will be corrected for multiple comparisons using the Benjamini–Hochberg False Discovery Rate (FDR) correction, with statistical significance set at alpha = 0.05 [51].

Pre-specified stratified and subgroup analyses will be undertaken. Given potentially divergent recovery trajectories between ischemic and hemorrhagic stroke, feasibility metrics and clinical outcomes will be reported separately for the ischemic and hemorrhagic subgroups, and where cell sizes permit, differences will be explored using exploratory between-subgroup comparisons (Mann–Whitney U tests for continuous outcomes and Fisher’s exact tests for proportions). Outcomes will likewise be summarized by baseline FMA-UE severity stratum (severe, 0–19; moderate-to-mild, 20–47) and, descriptively, by lesion location (cortical, subcortical, brainstem, or cerebellar). Because the feasibility sample (*n* = 12) is not powered for subgroup inference, all stratified analyses are explicitly exploratory and hypothesis-generating; they are intended to estimate the direction and variability of effects by stroke etiology and severity, will be reported with effect estimates and confidence intervals rather than an emphasis on *p*-values, and will inform pre-registered subgroup hypotheses for the future definitive trial.

Based on preliminary data from our meta-analysis of BCI rehabilitation in chronic stroke [24], we expect to observe improvements in FMA-UE scores with a mean change of approximately 5.23 points (standard error 0.70) by the end of 15 training sessions. Historical data from TTSH indicate a mean FMA-UE improvement from 29.1 to 37.4 points (+8.3 points) with standard rehabilitation [40]; thus, BCI may yield an expected total improvement of approximately 13–14 points if effects are additive.

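### The two FMA-UE severity strata stop at 47, so eligible participants and matched controls scoring 48–66 have no place in the exploratory severity-stratified analyses

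*Protocol article*

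**What the plan says.** Three sections of the protocol article define baseline severity by the same two bands.

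- Section 3.8 (stratified economic analysis): "1) severe impairment (FMA-UE 0–19) and (2) moderate-to-mild impairment (FMA-UE 20–47". The analysis will be stratified in this way, using cutoffs that the protocol describes as validated and cites to a published source.
- Section 3.12 (data analysis): "Outcomes will likewise be summarized by baseline FMA-UE severity stratum (severe, 0–19; moderate-to-mild, 20–47".
- Section 3.3 (historical controls), in softer terms: "FMA-UE categories may use severe impairment (FMA-UE 0–19) and moderate-to-mild impairment (FMA-UE 20–47".

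Section 1 describes the FMA-UE as having a "total score range 0 to 66, with higher scores indicating less impairment", and Table 1 gives the same range.

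In Section 2.3 the motor entry criterion is "demonstrated voluntary finger flexion or extension by Oxford Medical Research Council (MRC) grade 0–4/5". The arm-related exclusions cover pain, contracture, arthritis and "severe hemianesthesia or spasticity in the paretic arm (Modified Ashworth Scale greater than 2, out of 4". None of them is an upper limit on FMA-UE. Section 3.3 matches controls on baseline FMA-UE, also without a cap.

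Section 2.5 lists cost-effectiveness stratified by baseline severity as secondary hypothesis (iii). Sections 3.8 and 3.12 both call the stratified analyses exploratory.

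**The concern.** A set of strata should place every patient in exactly one category. These two do not: together they end at 47 on a scale that ends at 66. The upper band is labelled as reaching the mild end of impairment, yet it stops 19 points short. Finger strength of MRC grade 4 is admissible, so a patient with a baseline score above 47 can meet every stated criterion.

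Followed as written, the rule would give severity-stratified results that do not add up to the cohort. The patients left out would be those nearest the scale ceiling, who have the least room to gain FMA-UE points. The upper stratum's gain, and its cost per point if the Section 3.7 measure is reported by stratum, would then rest on a selected subset. The alternative is that the analyst decides where to put such patients after seeing the data, which fixing the cutoffs in advance is meant to prevent.

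This is not a detail left for an analysis plan. The protocol fixes the boundaries itself, and they do not fit the population it admits.

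**Working it through.** The protocol states no figure that could be reproduced here. The check is one of coverage, followed by an illustration of size.

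**Coverage.**
- Possible scores, 0 to 66: 67.
- Severe stratum, 0–19: 20 scores. Upper stratum, 20–47: 28 scores. Together: 48 of 67.
- Unassigned, 48–66: 67 − 48 = 19 scores, and 19/67 = 28%.

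**Can such patients enter?** Section 2.3 contains no FMA-UE minimum or maximum among either the inclusion or the exclusion criteria. Section 3.3 sets none for controls. No section says how a score of 48–66 is classified.

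**How many might there be?** Inputs:
- Baseline mean 29.1, from the historical local data in Section 3.12.
- Sample size, from Section 2.4: "the final proposed sample size is 12 participants".
- Baseline SD: not given in the protocol. Assumed range 10–20.
- Shape: assumed normal, with a continuity correction at 47.5.

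Formula: P(score > 47) = 1 − Φ((47.5 − 29.1)/SD) = 1 − Φ(18.4/SD). The truncated column restricts the normal curve to the scale, −0.5 to 66.5. The last column is 1 − (1 − p)^12, with p the truncated value.

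| Assumed SD | 18.4/SD | P(>47), plain normal | P(48–66), truncated | Expected of 12, truncated | Chance of at least one |
|---|---|---|---|---|---|
| 10 | 1.84 | 3.3% | 3.3% | 0.4 | 33% |
| 12 | 1.53 | 6.3% | 6.2% | 0.7 | 54% |
| 15 | 1.23 | 11.0% | 10.7% | 1.3 | 74% |
| 18 | 1.02 | 15.3% | 14.4% | 1.7 | 85% |
| 20 | 0.92 | 17.9% | 16.5% | 2.0 | 88% |

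Over both versions the range is about 3–18%, or about 0.4–2 of 12 participants. The chance that nobody scores above 47 runs from 67% (SD 10) down to 12% (SD 20).

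**Against what stratum size?** The expected number in 20–47 is 12 × [Φ((47.5 − 29.1)/SD) − Φ((19.5 − 29.1)/SD)]. With the plain normal this gives 8.7 at SD 12, 7.5 at SD 15 and 6.1 at SD 20, so about 6–9 of 12.

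**The case against.** The strongest reply concerns consequence, and most of it stands.

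- **Reach.** A reader might infer that mildly impaired participants drop out of every stratified analysis. The protocol does not support that. Section 3.12 also reports results by stroke type and by lesion location, and neither depends on FMA-UE. The feasibility benchmarks, the overall ICER and the overall cost per FMA-UE point are unstratified and keep everyone.
- **Intent.** A reader might also infer that the plan means to exclude these patients. No section says so; their classification is simply unstated.
- **Weight.** Section 3.8 calls the subgroup analyses strictly exploratory, Section 3.12 calls them hypothesis-generating, and Section 3.3 uses permissive wording for the categories. No primary endpoint, interim criterion or sample-size figure depends on the strata.
- **Size.** The SD is assumed, the normal shape is a convenience, and the historical cohort behind the mean of 29.1 may not resemble trial entrants. It would be too strong to set the loss against an upper stratum of about six: that size fits only the widest SD. It would also overstate the gap to call it a third of the scale.
- **Cited cutoffs.** The 20–47 band is attributed to a source that is not available here, so it cannot be said that 20–66 is the only proper upper band.

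These points limit the impact and widen the choice of remedy. They do not close the gap: Sections 3.8 and 3.12 say that the strata will be used, and even exploratory strata should place every patient.

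**Conclusion.** The point holds in a limited form. The severity strata leave FMA-UE 48–66 unassigned in all three sections that define them, while eligibility admits such scores. This follows from the text alone and rests on no assumption.

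The practical effect is confined to the exploratory severity-stratified economic analysis (Section 3.8) and outcome summaries (Section 3.12). About 0.4–2 of 12 participants would be affected, conditional on a mean of 29.1, an assumed SD of 10–20 and a roughly normal shape. None affected is a real possibility. If one or two are, the loss is noticeable beside an upper stratum expected to hold about 6–9 at SD 12–20. The change is worth making because it costs almost nothing now and would be a post hoc decision later.

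**What to change.** Before data are seen, make the strata exhaustive and identical in Sections 3.3, 3.8 and 3.12, so that every participant and every control belongs to exactly one. Either of two edits does this.

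1. Extend the upper stratum to FMA-UE 20–66. This keeps the 19/20 cutoff and two groups. The cost is that participants with ceiling-limited gains are pooled into the upper stratum: someone starting at 60 can gain at most 66 − 60 = 6 points, which affects that stratum's mean gain and cost per point.
2. Keep the cited 20–47 band and add a 48–66 category reported descriptively. The cost is a very small group, possibly empty, that supports no estimate of its own.

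Both are wording edits in three places and change nothing in recruitment or conduct. If a limit at 47 was intended for the study population, the eligibility criteria in Section 2.3 and the three stratum definitions contradict each other and must be reconciled by the sponsor.
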